#### Informed consent

Participants complete written informed consent to participate in this research. Consistent with Kenyan and U.S. law [44–46], local Kenyan and UCSD IRBs approved a waiver of parental consent for youth aged 15–17 years wishing to participate in the study after determining that the research poses no more than minimal risk to participants. This waiver protects adolescent girls seeking confidential reproductive health services at these clinics from a breach of confidentiality [45]. This waiver was also obtained to minimize any potential risk (e.g. retaliatory violence, expulsion from the home, or other harm) associated with breach of confidentiality to an abusive family members [47]. Completed and signed written informed consent forms will be stored in the Population Council’s Nairobi offices in a locked file cabinet until completion of data collection, after which time they will be destroyed.

### Data collection

#### Time points

Patients in both treatment and control groups will complete surveys at baseline (T1) prior to their clinical visit, immediately after their visit before exiting the clinic (exit survey), 12–16 weeks post-visit (3-month follow-up survey, T2), and 24–26 weeks post-visit (6-month follow-up survey, T3). RAs will be trained via a 5-day training, led by Population Council, that provides education on the ARCHES intervention, RC and IPV, responding to and referring participants that become upset during the interview, study protocols, and data collection forms. All surveys will be completed in-person via RAs reading all questions and responses aloud and recording responses using a tablet computer (Fig. 1. Study design; Table 1. Outcome measures).

#### Patient accrual and study flow

Six clinics, each treated as their own cluster, were matched-paired and allocated to a treatment group (3 intervention, 3 control). From each clinic, women will be approached for study recruitment; women will be excluded in the enrollment due to ineligibility or because they declined to participate, with the rest completing the baseline survey. See Fig. 1. Study design.

#### Re-contacting and retention

All patients that participated in the baseline survey, received contraceptive counseling, and completed the exit survey will be re-contacted to participate in a 3-month follow-up interview according to procedures designed to maximize participant retention. At the end of the 3-month follow-up survey, the RAs will schedule the 6-month interview and validate the patient’s contact information. All patients that participated in the baseline interview and met the eligibility criteria for inclusion in follow-up surveys will be re-contacted to participate in the 6-month follow-up interview, regardless of their participation at 3-months follow-up. Follow-up surveys will be conducted at the clinic where the participant was first enrolled into the study.

To maximize participant retention at follow-up surveys (T2 and T3), RAs will send text reminders approximately 4 weeks before their follow-up appointment to confirm contact and scheduling. Participants will also receive a text reminder the day before their appointment. If a participant is unreachable, RAs may attempt to reach them at their alternate contact (if provided). A maximum of five attempts will be made for each data collection point (T2 and T3). Participants that decline to participate will be asked why they are choosing to drop out of the study to inform loss to follow-up.

### Data analysis

We will adopt a difference-in-differences approach utilizing a multilevel, mixed-effects generalized linear regression, with logistic specifications for binary outcomes and linear specifications for continuous or scale outcomes, to evaluate associations between ARCHES intervention exposure and primary and secondary outcomes overtime. Longitudinal models will have fixed effects including time (baseline or follow-up), treatment arm, clinic, selected covariates, and a time and treatment interaction to indicate the treatment effect. These models will also take into account clusters (i.e. clinics) and clustering within clinics using nested random effects specifications to account for repeated measurements over time of individuals nested within clusters. The comparisons of outcomes at a single time point (e.g. immediately post-intervention) will use a similar multilevel mixed-effects regression approach, with single-level random effect specifications only for clinic, and only a fixed treatment effect (rather than time by treatment comparison). Final analyses will adjust for potentially relevant covariates (age, parity, food insecurity within the past 30 days, marital status, highest level of education attended, language of survey administration), in addition to time and treatment condition. Descriptive and bivariate analyses will be used to assess frequencies of and differences in demographics by treatment and loss to follow-up. Any characteristics identified as significantly associated with treatment or loss to follow-up at the *p* < 0.20 threshold will be considered as potential covariates (fixed effects) in adjusted models assessing effects of the intervention. Backwards selection at *p* < 0.20 will be used to finalize inclusion of potential covariates in regression models. Collinearity of covariates will be assessed, and highly collinear covariates may be removed from final models.

The primary analyses will use an intent-to-treat approach and analyze all subjects according to treatment group. Exploratory analyses will also be run stratified by age group (adolescent girls and young women age 16 to 24; adult women age 25 to 49). Missing data on demographics and birth history may be computed where alternate data is available (e.g. calculating age from date of birth if age is not provided); however, no missing data will be imputed. All scales to be used as outcomes will be assessed for internal reliability at baseline using exploratory factor analysis and Cronbach’s alpha. If scales are identified as multifactorial or not internally reliable, they may be modified to more accurately reflect the intended construct and/or be presented as individual item outcomes. An α level of 0.05 (i.e. 95% confidence intervals exclusive of one) will be considered the threshold for statistical significance in all analyses. Analyses will be conducted using STATA version 14.2® (StataCorp LLC, 2015) [48] and SAS version 9.4® (SAS Institute Inc., 2018) [49].

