### Study overview and design

We will test our hypotheses using a matched-pair, cluster-controlled design with the two parallel treatment groups assigned in a 1:1 allocation ratio (ClinicalTrials.gov ID: NCT03534401). Eligible female patients seeking contraceptive care services from clinics allocated to the intervention or control condition will complete surveys at baseline prior to their clinical visit (T1), immediately after their visit before leaving the clinic (T2; i.e. exit survey), 12–16 weeks post-visit (T3; i.e. 3-month follow-up survey), and 23–26 weeks post-visit (T4; i.e. 6-month follow-up survey). We designed this superiority trial with sufficient power (*N* = 600) to assess our hypothesized short (3-month) and longer-term (6-month) outcomes. See Fig. 1. Study design and Table 1. Outcome measures.

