### Power calculations and sample size

Based on the pilot data from 143 female FHOK patients ages 15–49 years, prevalence of RC within the past 12 months was estimated at 17.1%. In a large U.S. cRCT, clients receiving the ARCHES intervention experienced a 0.4 reduction in odds (equivalent to an 8 percentage point reduction in intervention group reporting) of RC during the prior 3 months [23]. The present study is designed to achieve 80% power to detect a reduction of this magnitude (OR 0.4) related to past 3-month RC experience. Calculations assumed three control and three intervention clusters. Cluster size was assumed to differ in the range of 50–250 individuals per cluster, with a mean number per cluster of 100; the coefficient of variation for cluster sizes was thus set at 0.5. We anticipated low intra-class correlation (ICC) based on previous ARCHES trials (ICC < 0.01%) [23]. To be somewhat more conservative, we assumed an ICC of 0.1%. Under these parameters, the required average cluster size was 68, for a total of 204 control and 204 intervention participants (total required *N* = 408) retained at final follow-up. In previous ARCHES trials, retention was > 90% at 3-months follow-up; we assumed 85% retention at 3-months follow-up relative to baseline and 75% retention at 6-months follow-up relative to baseline, for an initial minimum N of 544. Our target final sample of 600 individuals exceeds the sample size required based on this conservative calculation.

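### The difference-in-differences model has no clinic-by-time term, so a clinic-assigned effect is tested against woman-level variation, and the stated 80% power belongs to a different test

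*Protocol article*

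**What the plan says.** The protocol (Study overview and design) describes a "matched-pair, cluster-controlled design with the two parallel treatment groups assigned in a 1:1 allocation ratio". Assignment of clinics to treatment conditions says that assignment is by clinic, six in all in three pairs, and not random within pairs: clinics nearer the implementer's headquarters were more likely to be treated.

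The Data analysis section specifies the model for outcomes measured repeatedly, including reproductive coercion (RC) and intimate partner violence (IPV): "Longitudinal models will have fixed effects including time (baseline or follow-up), treatment arm, clinic, selected covariates, and a time and treatment interaction". That interaction is named as the treatment effect. Clustering is handled "using nested random effects specifications to account for repeated measurements over time of individuals nested within clusters". For outcomes at one time point, such as contraceptive uptake at exit, the model is similar, "with single-level random effect specifications only for clinic, and only a fixed treatment effect". On significance: "An α level of 0.05 (i.e. 95% confidence intervals exclusive of one) will be considered the threshold for statistical significance". Neither matched pair nor a clinic-by-time term appears in the model, and no reference distribution or degrees of freedom is named.

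Power calculations and sample size states: "The present study is designed to achieve 80% power to detect a reduction of this magnitude (OR 0.4) related to past 3-month RC experience". The planning rate comes from the pilot: "prevalence of RC within the past 12 months was estimated at 17.1"%. On the number of clinics, the section says: "Calculations assumed three control and three intervention clusters". The ICC is set at 0.1% and the coefficient of variation of cluster size at 0.5. The result is 68 retained women per clinic (408 in total, 544 enrolled), with a target of 600.

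**The concern.** A clinic intercept, fixed or random, is a constant for that clinic. It drops out of the change from baseline to follow-up, which is what the time-by-treatment interaction measures. What matters for the precision of that interaction is how much change itself varies from clinic to clinic, and the stated model has nowhere to put that variation. The interaction is then judged against variation within and between women, as if women rather than clinics had been assigned.

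With three clinics per arm, local differences in trend do not average out. The non-random assignment by distance makes such differences plausible. The RC and IPV results could look more certain than they are.

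The sample-size claim has a related problem. If 80% was computed for a comparison that is neither a difference-in-differences nor referred to six clinics, it does not describe the planned analysis.

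**Working it through.** **Inputs from the protocol.** Control RC rate 17.1% (a 12-month figure, taken as planned), OR 0.4, three clinics per arm, ICC 0.001, CV 0.5, two-sided 0.05 (implied by the 95% interval), 75% retention at 6 months.

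**1. Reproduce the stated figure.**
- Treated rate: odds 0.171/0.829 × 0.4 = 0.0825, so 0.0825/1.0825 = 7.62%. The difference is 0.0948.
- The two-proportion normal formula (pooled variance, 80% power) gives 188.1 women per arm before clustering, or 62.7 per clinic.
- Design effect: 1 + [(1 + 0.5²)m − 1] × 0.001. Solving for m: 62.7 × 0.999/(1 − 62.7 × 1.25 × 0.001) = 68.0. This matches the protocol's 68.
- 6 × 68 = 408, and 408/0.75 = 544. Both match.
- A continuity correction gives 76, a one-sided test 52–53, an 8-point difference 104–105, and a t test on 4 df about 126–130. So 68 is a z calculation on one follow-up time point.

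**2. Same inputs, reference distribution for six clinics.** At m = 68 the design effect is 1.084 and n = 204 per arm. SE = √[(0.171 × 0.829 + 0.0762 × 0.9238) × 1.084/204] = 0.0336. The noncentrality is 0.0948/0.0336 = 2.82. Critical values are 1.96 (z), 2.78 (t, 4 df) and 4.30 (t, 2 df).

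| Women per clinic | z | 4 df (unpaired) | 2 df (by pair) |
|---|---|---|---|
| 68 (required) | 80–81% | 57% | 36% |
| 75 (600 × 75%, over 6) | 84% | 61% | 38% |
| 100 (600, no loss) | 92% | 71% | 45% |

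For the same SE, intervals are 2.776/1.960 = 1.42 times wider on 4 df and 4.303/1.960 = 2.20 times wider on 2 df.

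**3. The planned estimand (change, not follow-up only).** On the logit scale the variance per woman is 1/[p(1 − p)]: v1 = 7.05 at 17.1% and v2 = 14.20 at 7.62%. With within-woman correlation r (assumed; not in the documents), the difference-in-differences variance is 2·v1(1 − r) + v1 + v2 − 2r√(v1·v2), multiplied by 1.084/204. The log OR is 0.916.

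| r | Variance sum | SE | 0.916/SE | z | 4 df |
|---|---|---|---|---|---|
| 0 | 35.37 | 0.433 | 2.11 | 56% | 37% |
| 0.3 | 25.13 | 0.365 | 2.51 | 71% | 48% |
| 0.5 | 18.30 | 0.312 | 2.94 | 84% | 60% |

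**4. Type I error when clinic-by-time variation is left out.** Null difference-in-differences data were simulated for six clinics (450 women in total, 17.1% prevalence). Clinic sizes were equal (75) or unequal, the between-women SD was 0 or 1.5 logits, and there were 4,000 to 20,000 runs per setting. The test was the difference in mean change with a woman-level SE. The ICC equivalent is roughly SD² × 0.171 × 0.829.

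| Clinic-by-period SD (logit) | ICC equivalent | Two-sided type I error |
|---|---|---|
| 0 | 0 | about 5% |
| 0.1 | 0.14% | about 6% |
| 0.2 | 0.57% | roughly 7–9% |
| 0.3 | 1.28% | roughly 10–15% |

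The ranges reflect differences in simulation set-up. A t test on clinic-level change stayed between 4% and 6% throughout. The simulated test stands in for the mixed model's interaction test; the mixed model itself was not fitted.

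**The case against.** The strongest reply is that the protocol names no test statistic or degrees of freedom, and a condensed article may leave these to an analysis plan that is not shown. That is right. A reader might infer that large-sample tests will be used on six clinics; the document does not say so for the analysis. It can be shown only for the sample-size figure. The missing random term is different, because the model itself is stated. Without that term a later small-sample rule would still give the interaction woman-level degrees of freedom.

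Second, the inflation is small on the protocol's own figure: about 6% near an ICC of 0.1%, and essentially nominal at the value below 0.01% reported from earlier trials. That also stands. The larger figures need clinic-by-period SDs that are assumptions. The protocol's ICC comes from the US trials and describes clustering of levels, not of change, so it does not settle the matter either way.

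Third, three further readings are tempting but not supported.
- **Aliasing.** Clinic fixed effects alias the arm main effect and make the random clinic intercept redundant, but the interaction remains estimable and is not biased by this.
- **Time coding.** Time coded as baseline or follow-up might suggest that 3 and 6 months are merged. It can equally mean one model per follow-up, which would fit the hypotheses.
- **Uptake.** Using 1.96 when 4 df apply gives 12.2% type I error, but only where clinic variance dominates. With a design effect near 1.08 that is a limiting case.

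Fourth, the 57% imposes a 4-df test that the protocol does not specify, and the difference-in-differences range adds an assumed correlation and carries the cross-sectional design effect over to change. These are fair limits on the exact numbers. Even with z, the planned estimand reaches 80% only towards the upper end of the correlations tried.

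**Conclusion.** The concern holds in conditional form. The stated longitudinal model omits the variance component that a clinic-level assignment requires for an effect on change, so its intervals are too narrow to the extent that change varies between the six clinics. How far is unknown: about one percentage point of extra type I error near the protocol's ICC, and two to ten points at assumed SDs of 0.2 to 0.3. The documents do not support a statement that the intervals are badly wrong.

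The power statement is on firmer ground. The arithmetic behind 68, 408 and 544 is internally correct, but it is for a follow-up-only z comparison with the ICC treated as known. For a test that estimates clinic variation from six clinics, the same inputs give 57% (4 df) or 36% (2 df) at 68 per clinic. For the difference-in-differences at 204 per arm the figures are 56–84% with z and 37–60% on 4 df, over assumed correlations of 0 to 0.5.

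**What to change.** In Data analysis:
- Remove clinic from the fixed effects, since arm is aliased with it.
- Add a clinic-by-time random term and base degrees of freedom on the number of clinics. Alternatively, make a two-stage analysis of clinic-level change the primary analysis. State whether it is unpaired (4 df) or keeps the matched pairs (2 df).
- The two-stage version is the safer of the two. A clinic-by-time variance estimated from six clinics will often come out at zero, and Kenward–Roger for binary outcomes relies on pseudo-likelihood, which can be biased with two or three measures per woman.
- Use the same clinic-level degrees of freedom for uptake.
- Say explicitly that effects are estimated separately at 3 and at 6 months.

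In Power calculations and sample size, replace the 80% with the power of the chosen test, showing the assumed within-woman correlation and a range of ICCs.

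The cost is wording and programming. Intervals become wider and the stated power falls; no extra enrolment is proposed.

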### Assignment of clinics to treatment conditions

As ARCHES facilitates changes in providers’ contraceptive service delivery to all female patients seen, individual random assignment of patients is not possible. Instead, assignment at the clinic level is required. All FHOK community-based clinics within and around the Nairobi area were enumerated (*N* = 6) by UCSD researchers and assigned to treatment or control condition in matched-pairs (*n* = 3 intervention, 3 control) by the UCSD and FHOK, with pairings determined based on those clinics most closely matched on patient volume, patient characteristics (i.e. wealth, age, services sought), and community type (slum vs non-slum). Random assignment within pairs was not acceptable to program implementers due to the reduced feasibility of providing regular support to ensure faithful, high-quality implementation to providers in distal clinics; i.e., those clinics closest to FHOK headquarters in southeast Nairobi were more likely to be assigned to the treatment condition. Participants self-assign to the treatment or control condition based on the clinic they visit for contraceptive services and enroll into the study by Population Council research assistants (RAs). No blinding of participants or providers will occur.

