#### Demographics and other potential confounders

Demographics and potential confounders will include age, parity, food insecurity, marital status, highest level of education attended, and language of survey administration. Age will be assessed as a continuous measure. Other measures will be categorical in nature. Parity will be classified as either having no live births, having one live birth, or having multiple live births. Past month food insecurity will be assessed as a binary (yes/no) item based on the question, “In the last 30 days, did you or any members of your household go without eating the whole day because there was not enough food?” Women both formally married and those cohabitating with a male partner will be considered married based on common practice. Highest level of schooling attended will be classified as primary or lower, secondary, or post-secondary.

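### As written, the covariate adjustment barely touches the difference-in-differences effects on RC and IPV, because no covariate is allowed to interact with time

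*Protocol article*

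**What the plan says.** Under Assignment of clinics to treatment conditions, the article states that "Random assignment within pairs was not acceptable to program implementers", that "those clinics closest to FHOK headquarters in southeast Nairobi were more likely to be assigned to the treatment condition", and that "Participants self-assign to the treatment or control condition based on the clinic they visit". The same section says the six clinics were paired on patient volume, on patient wealth, age and services sought, and on slum or non-slum community.

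The section on confounders states: "Demographics and potential confounders will include age, parity, food insecurity, marital status, highest level of education attended, and language of survey administration".

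Table 1 marks RC and IPV, two of the three primary outcomes, as change from baseline. The third, contraceptive uptake, is analysed as a single value at the exit survey.

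For the change outcomes, the Data analysis section says: "We will adopt a difference-in-differences approach utilizing a multilevel, mixed-effects generalized linear regression, with logistic specifications for binary outcomes". The longitudinal models have "fixed effects including time (baseline or follow-up), treatment arm, clinic, selected covariates, and a time and treatment interaction to indicate the treatment effect". Time by treatment is the only interaction listed, and covariates are described elsewhere in the section simply as fixed effects. The section then says that "Final analyses will adjust for potentially relevant covariates" and lists the same six variables. Candidates are screened for association with treatment or with loss to follow-up.

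**The concern.** The six variables are presented as potential confounders and are screened for association with treatment, so their purpose is at least partly to control confounding. In a difference-in-differences analysis, a covariate that affects only the level of the outcome does no harm, because each woman's baseline already removes it. The harmful covariate is one that differs between arms and also predicts how RC or IPV changes over follow-up. Removing its influence needs a term that lets the time trend vary with the covariate, and the stated model has none.

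If the model is fitted as described, the RC and IPV results would be reported as adjusted while being almost identical to the unadjusted ones. Had case mix differed between arms in a way that predicts change, part of that difference would appear as an ARCHES effect or would hide one. Uptake is not affected: in a single-time-point model, covariate main effects do adjust the treatment comparison.

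**Working it through.** The article gives no figure for this point, so there is nothing of the plan's own to reproduce. The check has four steps.

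**1. Algebra, linear case.** Let A be arm (0/1), t be time (0 baseline, 1 follow-up), x a baseline covariate and u the woman's random effect. The model as written (clinic terms act on level only and cancel in the same way) is

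Y = α + βt + δA + θAt + γx + u + e.

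Subtracting baseline from follow-up within a woman gives change = β + θA + (e₁ − e₀). The term γx has gone, so including or omitting it cannot alter the estimate of θ when data are complete. If the true trend also depends on x through a term λxt, omitting that term biases θ by λ × (mean of x in intervention − mean of x in control).

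**2. Worked example, true effect nil (assumed values).** Women under 25 are 60% of the intervention arm and 40% of control. Their RC falls from 25% to 15%, while older women stay at 12%.

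- Intervention: baseline 0.6×25 + 0.4×12 = 19.8%; follow-up 0.6×15 + 0.4×12 = 13.8%; change −6.0 points.
- Control: baseline 0.4×25 + 0.6×12 = 17.2%; follow-up 0.4×15 + 0.6×12 = 13.2%; change −4.0 points.
- Spurious difference in change: −2.0 points, which equals (0.6 − 0.4) × (−10).

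**3. The planned logistic form.** A random-intercept logistic model (woman-level SD assumed 1.8, 41-point quadrature) was fitted to the expected cell probabilities. Older women stay at 12% throughout. Entries are ratios of odds ratios; the truth is 1.

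| Young women, intervention/control | Their RC | No covariate | Main effect | Covariate-by-time |
|---|---|---|---|---|
| 55/45 | 25% to 15% | 0.916 | 0.916 | 1.00 |
| 60/40 | 25% to 15% | 0.839 | 0.839 | 1.00 |
| 65/35 | 28% to 14% | 0.699 | 0.700 | 1.00 |
| 40/60 (reversed) | 25% to 15% | 1.193 | 1.192 | 1.00 |

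Milder assumptions give less: 53/47 with the fall from 25% to 15% gives 0.949, and 55/45 with a fall from 20% to 15% gives 0.953.

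**4. Simulation with six clinic fixed effects, two waves and true effect nil.** One binary covariate had an assumed prevalence of 60% in intervention and 30% in control.

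- At N = 600 with complete data (150 replicates) and an assumed covariate effect on trend of −0.6 log-odds, the mean estimates were −0.244 with no covariate, −0.244 with a main effect and −0.063 with covariate-by-time. At −1.0 they were −0.294, −0.294 and −0.016. These averages carry Monte Carlo noise.
- The main effect moved the individual logistic estimates by about 0.001 on average and by 0.009 at most. In the linear version the largest movement was 3 × 10⁻¹⁵, which is rounding error.
- With covariate-dependent dropout (60% against 90% retained, N = 60,000), the main effect moved the estimate by 0.005 to 0.009. Bias of about −0.19 and −0.29 remained at the two trend settings.

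**The case against.** Several points on the other side have weight.

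- **Reading of the text.** A list introduced as including certain fixed effects need not be complete, an interaction is itself a fixed effect, and an analysis plan that is not shown could add terms. Even so, the article does write out the model and singles out one interaction. The natural reading is that no other is planned.
- **Covariates that change.** Food insecurity refers to the past 30 days, survey language belongs to an interview, and marital status can change. If these were re-measured and entered wave by wave, the interaction could move. The article does not say this is intended, and values measured after the visit could themselves be affected by treatment. The result above is for covariates held at baseline.
- **Other protection.** Pairs were matched on age, wealth, services sought and community type, and the within-woman contrast already removes level differences. Both reduce the risk, so covariate adjustment is not the only safeguard. Matching three pairs of clinics cannot be assumed to balance the women enrolled, and the article itself plans to test for differences by treatment.
- **Age strata.** Exploratory analyses by age group (16–24 and 25–49) would let the trend differ by age and so expose the worked example. They cover one covariate and are not the primary analysis.
- **Size.** The design targets an odds ratio of 0.4. With a standard error of about 0.38 for the 6-month log ratio (simulated at N = 600 with 85% and 75% retention), the bias at 60/40 is |ln 0.839| = 0.176, just under half a standard error. At 55/45 it is |ln 0.916| = 0.088, under a quarter.

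A reader might infer that the RC and IPV effects are confounded. The documents do not support that: they report no imbalance in any covariate and no differing trend. Main-effects difference-in-differences is also a recognised specification that relies on parallel trends.

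**Conclusion.** The point stands in a limited form. With covariates held at baseline and no covariate-by-time term, the promised adjustment leaves the RC and IPV interaction practically unchanged, and exactly unchanged only in a linear model with complete data. That property of the model does not depend on the assumed scenarios.

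Whether bias follows is a separate matter. It needs a covariate that both differs between arms and predicts change. Non-random allocation makes this plausible and matching makes it less likely; the documents settle neither. Under the assumptions in the working, a true null would appear as a ratio of odds ratios from about 0.92 to 0.70, or as about 1.19 with a 60/40 imbalance reversed. Weaker imbalances or trends give values closer to 1.

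Two stronger conclusions might be drawn: that adjustment does nothing anywhere, or that the primary analysis is invalid as planned. Neither is supported. Main effects do adjust uptake, and the scale of any bias for RC and IPV is assumed rather than documented. This should be fixed because the improvement is real and inexpensive, but it is not a fatal defect.

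**What to change.** In every longitudinal model, hold the six named covariates at their baseline values and include each one's interaction with time. Take the treatment effect from that model and report the main-effects version as a sensitivity analysis. Prespecify this before outcomes are analysed by arm. State as well that these terms address measured trend differences only, and that unmeasured clinic-level trends, with three non-randomised clinics per arm, remain.

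The cost is analysis wording, with no new data. It adds up to about 8 parameters per follow-up time (age 1, parity 2, food insecurity 1, marital status 1, education 2, language 1), so 16 if the 3- and 6-month surveys are modelled separately. In a check at N = 600 with 85% and 75% retention, 16 such terms raised the standard error of the 6-month log ratio from about 0.38 to 0.39, which is 0.39/0.38 − 1, or about 3%. RC and IPV are binary and may be sparse; if events are too few, use one common follow-up interaction per covariate, which halves the added terms.
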